### Objectives

The objective of the CHAMPS Study and Registry is to assess the short- and long-term physical, social, and behavioral health of personnel (“essential workers”) involved in supporting or delivering care for patients with COVID-19. Included are first responders, maintenance and support staff working in clinical settings, and health care professionals of all specialties and services. At enrollment, baseline data were obtained on the study participants’ working environment, lifestyle, and mental and physical health. Subsequent waves of data collection will obtain follow-up information after 6 months and then annually through 2024. The study was approved by the Villanova University Institutional Review Board (IRB) in May 2020.

The primary objectives of the CHAMPS study are to (1) determine the extent to which working in health care affects future physical and mental health; (2) evaluate trends over the time course of the evolving pandemic; (3) identify exposure variables that are associated with incident changes in health over time; and (4) identify factors that influence short- and long-term health. Specific hypotheses include the following:

Measures of mental health symptoms of anxiety, traumatic stress, depression, insomnia, disordered eating, resilience, burnout, and poor self-reported health will be more prevalent in essential workers than in the general population and greater in magnitude than reported in similar populations before the COVID-19 pandemic.The severity of mental health symptoms will be associated with prevalence of SARS-CoV-2 infection rates in the geographic region in which the study participants work.Mental health symptoms will persist longer among study participants with more severe symptoms.Essential workers who report elevated symptoms of anxiety, traumatic stress, or depression will experience exacerbation of existing physical health conditions over time and higher incidence of new physical health conditions.Severity and progression of mental and physical health conditions will be exacerbated by the degree of perceived exposure to adverse working environments, such as availability of personal protective equipment, extended working hours, and adequacy of staffing levels.

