### Participants and Recruitment

Eligible participants were adult essential workers involved in health care. For the purposes of the CHAMPS study, essential workers were defined as adult (aged 18 years or older) health care personnel, support personnel, and first responders working in any health care facility or in the community. Included were those working in facilities that are involved in patient care, such as hospitals, clinics, private practices, or screening facilities; those directly involved in patient care (eg, physicians, nurses, phlebotomists, respiratory therapists, pharmacists); laboratory staff; service employees (office staff, maintenance, housekeeping, food service); individuals working in long-term care facilities; and first responders (eg, police officers, firefighters, emergency medical technicians, paramedics). Collectively, we refer to these as “essential workers.” Enrollment took place over 13 months, from May 2020 through June 2021, throughout the United States.

Recruitment included advertising through local and national professional and trade organizations, news, social and professional media, alumni organizations, and word of mouth to describe the study and disseminate the internet link that provided access to the informed consent form and study questionnaires. Professional and trade organizations were identified and contacted. Website posts, e-newsletters, and social media were used to reach members of eligible occupations, with news or social media posts either by their group administrators or by the study team. The wider social media universe was reached through posts on university channels on various platforms, university-affiliated influencer posts, and a limited paid media campaign. Social media posts and outreach to organization leaders continued periodically throughout the recruitment period.

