### Exposure Assessment

We will define and quantify exposure to COVID-19 service burden by summing participants’ scores on the Perception of Stress at Work scale developed by Wu and colleagues [4] in 2009 during the SARS pandemic, and we will add a point to that score for each of several additional stressors: (1) working more hours since the pandemic; (2) working in a different setting; (3) caring for patients with COVID-19; (4) changing one’s living arrangement; (5) receiving a COVID-19 diagnosis; and (5) having a close contact (friend, family member, colleague, or any loved one) with a COVID-19 diagnosis (Table 2).

For this purpose, perceived stress was deemed to be an outcome of exposure, but it can also be included as an exposure variable in models that ascertain incidence of health conditions over time.

**Table 2 table2:** Components of the algorithm-based score for exposure to COVID-19 service burden.

Component	Scoring
Perception of Stress at Work scale	Score of 9-item scale
Working more hours	Yes=1 additional point
Working in a different setting	Yes=1 additional point
Caring for patients with COVID-19	Yes=1 additional point
Changing one’s living arrangement	Yes=1 additional point
Receiving a COVID-19 diagnosis	Yes=1 additional point
Having close contact (friend/family member/colleague/any loved one) with a COVID-19 diagnosis	Yes=1 additional point

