### Analysis

#### Data Management and Quality

Data are collected through the web-based Qualtrics system. SPSS (IBM Corporation) and SAS (SAS Institute, Inc) will be used for data analysis. Initially, we will perform an exploratory analysis to establish patterns of missingness and distributions of the variables being measured. The registry data will be characterized with descriptive analyses, including frequency distributions, prevalence rates of COVID-19 testing and SARS-CoV-2 infection, and means and standard deviations of scores on the scales measuring work environment, general health status, anxiety, depressive symptoms, social support, traumatic stress, social support, sleep quality, and stress. Multiple logistic and linear regression methods will be used to assess baseline associations of health and well-being with estimates of exposure to COVID-19 infection and COVID-19–related stress at work. Models will be adjusted for sex, age, race/ethnicity, and job classification. Other preliminary explorations of associations between measured variables will be performed to aid the development of substudies from the registry. Follow-up health status questionnaires will enable analysis of associations between incident health events and baseline variables.

Narrative responses to the final question on the questionnaire will be analyzed using a deductive approach and thematic content analysis techniques. Multiple investigators will read the narratives provided by participants to perform coding of the significant statements made by participants. After multiple readings, investigators will generate data categories and clusters of statements and will develop themes.

#### Aim 1

We will determine whether essential workers with higher COVID-19 service exposure burden will experience higher rates of stress, depression, anxiety, and substance use than the general population at the time they enroll in CHAMPS, and higher than in similar populations before the COVID-19 pandemic. We will compare exposure by type of service, occupation, and place of service (eg, clinical setting or community), controlling for age, self-reported sex, and race. We will conduct analyses to identify mediators, such as racial status, and moderators, such as proactive coping and resilience.

#### Aim 2

We will determine whether the severity of mental health symptoms will be associated with changes in the prevalence of SARS-CoV-2 infections by geographic region.

#### Aim 3

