### Limitations

This is a convenience sample, which limits the generalizability of the results to the entire population of essential workers. Some occupation categories will have small sample sizes; thus, we may not have sufficient representation for individual analyses. Self-selection bias may also be a factor if some individuals decline to participate due to reluctance to be perceived as not supportive of their institutions. The measurement of COVID-19 service exposure relies on an algorithm that should be evaluated against an independent data set. Finally, the planned longitudinal analyses will depend on retaining a sufficient proportion of participants over time.

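### Aim 1 sets higher-burden workers, not all workers as in Hypothesis 1, against an unselected general population, and Objective 1 states an effect of working in health care that the cohort cannot estimate

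*Protocol article*

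**What the plan says.** **External comparison.** Hypothesis 1 (Objectives) holds that the symptom measures "will be more prevalent in essential workers than in the general population and greater in magnitude than reported in similar populations" before the pandemic. It places no burden restriction on the workers. Aim 1 (Analysis) asks instead whether "essential workers with higher COVID-19 service exposure burden will experience higher rates of stress, depression, anxiety, and substance use than the general population" show this excess "at the time they enroll in CHAMPS, and higher than in similar populations before the COVID-19 pandemic".

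**Burden score.** Exposure Assessment and Table 2 build the score from the Perception of Stress at Work scale ("Score of 9-item scale") plus one point for each of six further items: more hours, a different setting, caring for COVID-19 patients, a changed living arrangement, own diagnosis, and a close contact's diagnosis. The same section calls perceived stress an outcome of exposure.

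**Objective 1.** The first primary objective is to "determine the extent to which working in health care affects future physical and mental health". Under Participants and Recruitment, "Eligible participants were adult essential workers involved in health care".

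**Limitations.** The article states: "This is a convenience sample, which limits the generalizability of the results to the entire population of essential workers". It does not mention the lack of a group outside health care.

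**The concern.** Hypothesis 1 and Aim 1 define different contrasts, and nothing in the article reconciles them. In Aim 1 the worker group is limited to its more burdened members, while the general population keeps its full range, including its own highly stressed members. The limiting score rests largely on reported stress, and stress is one of the four outcomes. A positive Aim 1 result could then be read as support for Hypothesis 1 when it reflects only who was placed on the worker side.

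Objective 1 has a related problem. It attributes later health to working in health care, a factor on which the cohort does not vary. A reader of the final report could take within-cohort associations as evidence of an effect that was never contrasted with anything.

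**Working it through.** The article gives no effect size, power or sample-size calculation, so there is no stated figure to reproduce. The check has two parts.

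**1. What the Aim 1 restriction does when workers overall do not differ**

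Input from the article: 2762 enrolled (Results), so the top half by burden is 2762/2 = 1381.

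Assumptions, because the article gives no values:
- correlation r between burden score and symptom score, 0 to 0.5;
- higher burden means the top half, or the top third as a sensitivity case;
- general-population prevalence 10% or 20%;
- burden and symptom are bivariate normal, and all workers together have exactly the population's symptom distribution, so the true difference is zero.

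Formulas, for the top fraction q with cut c = z(1−q) and symptom threshold t:
- mean shift = r × φ(c)/q; for the top half, φ(0)/0.5 = 0.399/0.5 = 0.798, so the shift is 0.798 × r;
- prevalence in the group = P(symptom > t and burden > c)/q.

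| r | Mean shift, top half | 10% becomes | 20% becomes |
|---|---|---|---|
| 0 | 0 | 10.0% | 20.0% |
| 0.1 | 0.08 SD | 11.4% | 22.2% |
| 0.2 | 0.16 SD | 12.8% | 24.5% |
| 0.3 | 0.24 SD | 14.2% | 26.7% |
| 0.5 | 0.40 SD | 16.8% | 31.3% |

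For the top third, r of 0.1 to 0.5 gives shifts of 0.11 to 0.55 SD, and 10% becomes 12% to about 21%.

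The halves balance. At r = 0.3 the lower half has 5.8%, and (14.2 + 5.8)/2 = 10.0%. With all workers, as in Hypothesis 1, the difference in this model is zero for every r.

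At n = 1381, a two-sided 0.05 test against a fixed external rate would declare an excess with probability 2.5% at r = 0, 42% to 55% at r = 0.1, and 91% to 98% at r = 0.2 (the ranges cover the two prevalences). These are false findings only if the result is taken to describe workers overall.

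On the sign of r, the fifth hypothesis under Objectives expects mental and physical conditions to worsen with perceived exposure to adverse working conditions. The protocol itself therefore expects r above zero.

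**2. What contrast Objective 1 has**

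- Eligibility admits only essential workers involved in health care, so nobody lies outside the factor named in the objective.
- The general population is named in Hypothesis 1 and, in Aim 1, at enrolment. No outside comparator is named for follow-up outcomes.
- Aims 3 and 4 relate later health to burden, type of service and symptom severity among participants.
- The longitudinal group is 1534 of 2762 (55.5%), all of them essential workers.

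The data can therefore support gradients within the cohort, but not a contrast between working and not working in health care.

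**The case against.** The strongest reply is that much of the right analysis is already planned. Hypothesis 1 still states the whole-group comparison. Data Management and Quality plans baseline regressions on exposure and work stress, adjusted for sex, age, race/ethnicity and job classification. Aim 1 also compares exposure by service, occupation and place, and Aim 3 follows the burden gradient over time. No section sets a burden cut, so Aim 1's sentence may simply merge a gradient with an external comparison. All of this stands. It makes the repair cheap, but it leaves the two stated contrasts in conflict.

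Three stronger readings are tempting and are not supported:
- *That Aim 1 must show an excess.* For depression, anxiety and substance use this depends on a positive correlation; at r = 0 there is none. For stress, the article does not say which measure Aim 1 means. If it is the Impact of Events Scale, the link to the burden score is correlation, not identity.
- *That a positive Aim 1 result would be false.* If burden and symptoms are correlated, higher-burden workers really are more distressed. The error lies in carrying that result over to all workers.
- *That Objective 1 has no analysis behind it.* Aim 3 gives it one, and involvement in care varies, since office staff, housekeeping, police and firefighters are eligible. What is missing is an outside group, and the planned longitudinal analyses do not rely on one.

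The choice of cut and of reference dataset may properly sit in an analysis plan that is not shown, and their absence is not criticised here.

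**Conclusion.** The point holds in this form. Aim 1 and Hypothesis 1 state different external contrasts, and Aim 1's version favours an excess whenever burden and symptoms are positively correlated. Its size is illustrative only: for the top half and r of 0.1 to 0.5, a 10% prevalence becomes about 11% to 17% with no difference among workers overall. The correlation, cut, prevalence and normal model are all assumed. Objective 1 as worded is not estimable from this cohort; associations with burden, service type and occupation are. Both faults lie in what the article states. They should be fixed, but they do not undermine the within-cohort analyses, and the disclosed convenience-sample limitation addresses a different matter.

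**What to change.** (a) **External comparison in Aim 1.** Use all enrolled workers, as in Hypothesis 1, standardised to the reference population's age, sex and race. Keep the pre-pandemic comparator. Report the result descriptively with the convenience-sample caveat, for outcomes measured at baseline: stress, depression and anxiety. Drop substance use from this baseline contrast, because Table 1 collects it only at 6 months, and the Alcohol and Substance Use section records it only as increased, unchanged or decreased.

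(b) **Burden.** Analyse it as a separate within-cohort gradient with lower burden as reference. Where the outcome is stress, use the six single-point items of Table 2 without the Perception of Stress at Work scale.

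(c) **Objective 1.** Reword it along these lines: *how far the degree of COVID-19 service burden among essential workers is associated with their later physical and mental health*.

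**Cost.** Rewording plus a standardisation step, with no new data collection from participants. The headline claim becomes narrower, and the external difference will probably be smaller.

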We will ascertain whether exposure to COVID-19 service burden will affect physical and mental health over time and how these are influenced by psychosocial variables (eg, stress, depression, anxiety, burnout). We will analyze whether longitudinal health outcomes are associated with type of service; severity and duration of mental health symptoms; and age, sex, race, and other variables. We anticipate that some analyses will depend on the adequacy of the sample sizes in various demographic subgroups.

#### Aim 4

We will obtain longitudinal data to determine whether mental health symptoms will persist longer among participants with more severe symptoms and whether these symptoms will be associated with higher incidence of physical health conditions.

#### Aim 5

We will ascertain the extent to which the thematic contents of the narrative responses to the final question of the questionnaires are correlated with measures of distress (stress, anxiety, depression, burnout) and moderated by measures of resilience. We will ascertain whether thematic content is a moderator or mediator of health outcomes and is associated with retention of participants over time.

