## Results

A review of the published literature on relationships between stressful life events and health led to the hypothesis that stress experienced by essential workers during the COVID-19 pandemic would affect their health status over time. In response, CHAMPS was designed to ascertain work-life experience during the first year of the pandemic, exposure to stress, and self-reported mental and physical health, as well as to determine effects of service during the pandemic on health over the subsequent 5 years. The CHAMPS longitudinal cohort serves as a registry for recruiting participants in future ancillary studies. After IRB approval, 2762 participants were enrolled between May 2020 and June 2021, with 1534 providing contact information for future studies and follow-up questionnaires.

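### Aim 1 names race as a mediator of COVID-19 service burden; race precedes the burden and can be a confounder or an effect modifier, but not a mediator

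*Protocol article*

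**What the plan says.** The mediator sentence is in the protocol article, Analysis, Aim 1: "We will conduct analyses to identify mediators, such as racial status, and moderators, such as proactive coping and resilience". It uses mediator and moderator as separate terms, places race with the mediators, and names no other mediator.

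The exposure in Aim 1 is service burden. The aim asks whether "essential workers with higher COVID-19 service exposure burden will experience higher rates of stress, depression, anxiety, and substance use". The Exposure Assessment section explains how burden is built: "We will define and quantify exposure to COVID-19 service burden by summing participants’ scores on the Perception of Stress at Work scale", plus one point for each of six stressors listed in Table 2.

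Race appears in three other places in the analysis text, each time as a background variable:

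- In the general paragraph (Data Management and Quality), for baseline associations of health with exposure: "Models will be adjusted for sex, age, race/ethnicity, and job classification".
- In Aim 1, for the comparison of exposure between kinds of service, jobs and settings: "controlling for age, self-reported sex, and race".
- In Aim 3, among the variables to be related to longitudinal outcomes: "severity and duration of mental health symptoms; and age, sex, race, and other variables".

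**The concern.** Mediation analysis asks how much of an exposure's effect passes through an intermediate variable. That has meaning only if the exposure can alter the intermediate. Race is fixed before any pandemic service begins, so nothing in the burden score can alter it.

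Running the analysis anyway would still produce a number. That number would measure how far the burden-symptom association is confounded by race, yet it would be described as race explaining how burden harms health. In a study that sets out to inform public health policy, this is a misleading statement about race. The answerable question, whether burden has a different effect in different racial or ethnic groups, is a question about moderation.

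**Working it through.** The article gives no figure on this point, so there is none to reproduce. The check has two parts: causal order, then what the analysis would yield.

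**1. Causal order under each plausible reading**

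- *Exposure is service burden* (the Aim 1 wording). Its components are perceived stress at work, longer hours, a changed setting, care of COVID-19 patients, changed living arrangements, own diagnosis and a close contact's diagnosis. None can change race.
- *Exposure is occupation or place of service.* Race still comes first.
- *Race is the starting point and burden the intermediate.* Then burden is the mediator, not race.

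The article nowhere redefines racial status as something modifiable, such as experienced discrimination. No reading makes race a mediator.

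**2. What a mediation analysis would return**

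Let E be burden, R race (0/1) and Y a symptom score. With ordinary least squares on the same participants:

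- crude slope of Y on E = c
- slope of E in the model for Y on E and R = c′, and coefficient of R in that model = b
- slope of R on E = a
- identity: c − c′ = a × b

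The product a × b is the usual estimate of an indirect effect. When R precedes E, it is the bias from leaving R out, that is, confounding by race.

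**3. Illustrative size**

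The only input from the document is the sample size ("2762 participants were enrolled between May 2020 and June 2021"). The following are assumptions: minority share p = 25%, burden higher by d = 0.3 to 0.5 SD in that group, symptoms higher by b = 0.2 to 0.4 SD, SDs of about 1, and complete data.

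- a ≈ p(1 − p) × d
- Low case: a = 0.1875 × 0.3 = 0.056; a × b = 0.056 × 0.2 = 0.011
- High case: a = 0.1875 × 0.5 = 0.094; a × b = 0.094 × 0.4 = 0.038
- Low-case standard errors: se(a) = √(0.1875/2762) = 0.0082; se(b) = 1/√(2762 × 0.1875) = 0.044
- Sobel SE = √(0.056² × 0.044² + 0.2² × 0.0082²) ≈ 0.0030; z = 0.011/0.0030 ≈ 3.8 (unrounded inputs)

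Varying the share changes little. At 20% the low case is 0.16 × 0.3 × 0.2 = 0.0096; at 30% the high case is 0.21 × 0.5 × 0.4 = 0.042.

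**4. Simulation** (n = 2762, 1000 runs per row, linear models, Sobel test at 1.96, all effects assumed)

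| Minority share | Race→burden (SD) | Race→outcome (SD) | True burden effect | Crude | Adjusted | Product a × b | Significant |
|---|---|---|---|---|---|---|---|
| 0.2 | 0.5 | 0.5 | 0 | 0.038 | −0.001 | 0.039 | 100% |
| 0.2 | 0.5 | 0.5 | 0.3 | 0.339 | 0.300 | 0.039 | 100% |
| 0.2 | 0.3 | 0.3 | 0.3 | 0.314 | 0.300 | 0.014 | 99.9% |
| 0.3 | 0.5 | 0.5 | 0 | 0.049 | −0.001 | 0.050 | 100% |
| 0.2 | 0 | 0.5 | 0.3 | 0.300 | 0.300 | 0.000 | 3.6% |

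In every run the product equalled crude minus adjusted to machine precision. In rows 1 and 4 burden does nothing, yet mediation by race is declared in every run. Adjusting for race recovers the true burden effect in every row.

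**The case against.** The strongest defence is that this is one example in an exploratory sentence, perhaps a slip for moderators, and that no main estimate depends on it. That limits the severity but does not remove the error: as written, the sentence sets the two terms apart and puts race on the wrong side. A slip still needs correcting. An analysis plan may add method, but it should not have to reverse a role that the protocol assigns.

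A reader might infer four stronger points, which the document does not support.

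- *That the article contradicts itself by holding race constant and analysing it as a mechanism.* The Aim 1 phrase on controlling for race governs a comparison of exposure, which has a different dependent variable. Adjusting for a variable in one model and examining it as a mediator in another is not in itself inconsistent, and a mediation model includes the mediator anyway. The other passages show only that race is elsewhere given a background role.
- *That the article commits to reporting an indirect effect.* It names no mediation method and no such quantity. The consequence follows from the wording; it is not a stated output.
- *That the crude-minus-adjusted identity holds throughout.* It is exact for linear models only. The article also plans logistic regression, where odds ratios are non-collapsible and the identity fails.
- *That effect modification by race will go untested.* The lists in Aim 1 are introduced as examples, and Aim 3 and the Discussion anticipate demographic analyses. None promises a burden by race interaction, but none excludes one.

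**Conclusion.** The concern holds in a limited form. The role assigned to race in Aim 1 is wrong as written, whatever the numbers. A result from that analysis would be confounding by race reported as a mechanism.

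The size of 0.01 to 0.04 SD per SD of burden (up to 0.05 in the simulated cases) is illustrative. It rests on assumed group shares and differences, linear models and complete data on all enrolled participants. It is small, and the z of about 3.8 reflects the large sample rather than great harm. If race is unrelated to burden, the spurious effect vanishes.

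The baseline health models adjust for race/ethnicity, so the main associations are not affected by this error. It should be fixed, but it is not critical.

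**What to change.** In Aim 1, delete racial status as the example of a mediator. Keep race/ethnicity as an adjustment covariate and name it as a candidate moderator, tested by a burden × race/ethnicity term and reported as group-specific estimates with intervals.

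Reserve the word mediator for variables that arise after the exposure and are not part of the burden score. This excludes the Perception of Stress at Work scale, because Table 2 makes it a component of that score. Aim 1 concerns outcomes at enrolment, so a mediator measured at follow-up belongs with the longitudinal aims, where at most 1534 of the 2762 participants gave contact details.

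The cost is one edited sentence and one interaction term, with no new data. The drawback is wide intervals in small race/ethnicity groups, in line with the article's own caution about subgroup sample sizes.

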### Measures

The baseline questionnaire consisted of questions related to the participants’ demographic information, occupation, and work environment, followed by validated instruments on behavioral health, described below. Instruments were selected to balance validity and brevity. An open-ended question provided an opportunity to describe personal experiences of working during the COVID-19 pandemic and participants’ interest in being interviewed. The measures and timepoints of data collection are outlined in Table 1.

**Table 1 table1:** COVID-19 Study of Healthcare and Support Personnel (CHAMPS) measures and data collection timepoints. All data are self-reported.

Measure	Instrument	Items, n	T0 (baseline)	T1 (6 months)	T2 (Year 1)	T3 (Year 2)	T4 (Year 3)	T5 (Year 4)
Demographics	N/A^a^	N/A	✓					
Anxiety	GAD-7^b^	7	✓		✓	✓	✓	✓
Depression	PHQ-2^c^	2	✓		✓	✓	✓	✓
Social support	OSSS-3^d^	3	✓					
Sleep	ISI-7^e^	7	✓		✓	✓	✓	✓
Traumatic stress	IES-R^f^	22	✓		✓	✓	✓	✓
Stress specific to COVID-19	Based on Wu et al [4] and Chong et al [5]	10	✓					
Resilience	BRS^g^	6		✓	✓	✓	✓	✓
Proactive Coping	Proactive Coping Subscale of the PCI^h^	14		✓				
Burnout	OLBI^i^	16		✓	✓	✓	✓	✓
Eating habits	LOCES^j^	7		✓	✓	✓	✓	✓
Morphometric	Height, weight	2		✓				
Alcohol and substance abuse	N/A	2		✓				
Physical activity	N/A	2		✓				
Health history checklist	N/A	14		✓	✓	✓	✓	✓

^a^N/A: not applicable.

^b^GAD-7: Generalized Anxiety Disorder-7.

^c^PHQ-2: Patient Health Questionnare-2.

^d^OSSS-3: Oslo Social Support Scale-3.

^e^ISI-7: Insomnia Severity Index-7.

^f^IES-R: Impact of Events Scale - Revised.

^g^BRS: Brief Resilience Scale.

^h^PCI: Proactive Coping Inventory.

^i^OLBI: Oldenburg Burnout Inventory.

^j^LOCES: Loss of Control Over Eating Scale.

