#### Six-Month Follow-up

The first follow-up occurred 6 months after enrollment and completion of the baseline questionnaire. Assessments included resilience, burnout, eating habits, and alcohol and substance use; physical activity; nutrition; height, weight, and weight discrimination items [41,42]; and a comprehensive health history checklist.

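### Aim 1 seeks mediators of enrolment outcomes from data that carry no mediator-outcome time order, and the one mediator it names, race, precedes the exposure

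*Protocol article*

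**What the plan says.** All references are to the protocol article.

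- **Outcomes (Analysis, Aim 1).** Workers with a higher service burden are expected to show "higher rates of stress, depression, anxiety, and substance use than the general population at the time they enroll in CHAMPS".
- **Mediation (Aim 1, same paragraph).** "We will conduct analyses to identify mediators"; the only example given is racial status. The same sentence gives proactive coping and resilience as examples of moderators. The comparisons by service, occupation and place are made "controlling for age, self-reported sex, and race".
- **Baseline timing (Measures).** "The baseline questionnaire consisted of questions related to the participants’ demographic information, occupation, and work environment, followed by validated instruments on behavioral health". Table 1 ticks anxiety (GAD-7), depression (PHQ-2), social support (OSSS-3), sleep (ISI-7), traumatic stress (IES-R) and COVID-19 stress at T0.
- **Six-month timing (Six-Month Follow-up).** "Assessments included resilience, burnout, eating habits, and alcohol and substance use". Table 1 has no T0 tick for these, nor for proactive coping.
- **Exposure (Exposure Assessment).** The burden score is a self-reported scale of stress at work plus up to six one-point items. The section treats perceived stress as an outcome of exposure but also allows it as an exposure in incidence models.

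**The concern.** A mediator has to be affected by the exposure and then affect the outcome. To support that reading, the data need some time order, above all between mediator and outcome. Aim 1 places the search for mediators next to outcomes set at enrolment, and for those outcomes the schedule gives no such order.

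If anxiety disturbs sleep, a mediation model that puts sleep between burden and anxiety will still return an indirect effect. The paper could then describe a consequence of anxiety as a route to it. This matters because studying mediators is part of the stated objective in the abstract, and because the registry is expected to feed ancillary studies that include wellness interventions.

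The named example has a separate fault. Race cannot be changed by service burden, so it cannot lie on a path from burden to symptoms, and the same aim already adjusts for it.

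**Working it through.** The article gives no power, effect size or correlation for Aim 1, so there is no figure to reproduce. The check has three parts.

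**1. Timing, from Table 1 and the Six-Month Follow-up section**

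| Role in Aim 1 | Variables | First measured |
|---|---|---|
| Exposure | stress at work and added items | T0 |
| Outcomes | stress, anxiety, depression | T0 |
| Outcome | substance use | T1 only |
| Possible mediators | sleep, social support, traumatic stress | T0 |
| Possible mediators | burnout, eating habits | T1 |
| Named mediator | race | fixed before exposure |

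For stress, anxiety and depression at T0, no candidate is measured after the exposure and before the outcome.

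**2. Can the data tell the orders apart?** Let X be burden, M the candidate mediator and Y symptoms, all standardized. The indirect effect for X>M>Y is

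rXM × (rMY − rXY × rXM) / (1 − rXM²).

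The other orders follow by exchanging roles. In one simulated data set with n=2762, the three just-identified models X>M>Y, X>Y>M and Y>M>X each had log-likelihood −11140.09. Fit therefore cannot choose between them. The size of the indirect effect does differ (assumed correlations):

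| rXM, rMY, rXY | X>M>Y | X>Y>M | Y>M>X |
|---|---|---|---|
| 0.3, 0.5, 0.3 | 0.135 | 0.135 | 0.100 |
| 0.3, 0.5, 0.15 | 0.150 | 0.070 | 0.150 |
| 0.3, 0.3, 0.2 | 0.079 | 0.050 | 0.079 |
| 0.4, 0.6, 0.3 | 0.229 | 0.158 | 0.206 |
| 0.2, 0.5, 0.4 | 0.088 | 0.200 | 0.000 |
| 0.3, 0.6, 0.1 | 0.188 | 0.058 | 0.225 |

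At n=2762 the Sobel z for the swapped order X>Y>M runs from 5.2 to 17.7 across these rows.

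**3. How often would a wrong order look like mediation?** Suppose X affects Y, Y affects M, and M has no effect on Y. Write r = rXY and s = rMY, so that rXM = rs. Fitting X>M>Y then gives

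- a = rs, with SE(a) = √[(1 − a²)/(n − 2)];
- b = (s − r × rs)/(1 − r²s²);
- apparent proportion mediated = ab/r = s²(1 − r²)/(1 − r²s²).

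Weakest setting, r=0.1 and s=0.3:

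- a = 0.03, and SE(a) = √(0.9991/2760) = 0.0190.
- b = 0.297/0.9991 = 0.2973, with SE(b) = 0.0181.
- ab = 0.0089, and its Sobel SE is √(0.03² × 0.0181² + 0.2973² × 0.0190²) = 0.0057.
- z = 1.57, so the chance of significance is about Φ(1.57 − 1.96) = 35%.

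Strongest setting, r=0.3 and s=0.6: a = 0.18, b = 0.546/0.9676 = 0.564 and z is about 9.3, so practically every cohort is significant.

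Apparent proportion mediated at the four corners:

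- r=0.1, s=0.3: 0.0891/0.9991 = 8.9%
- r=0.3, s=0.3: 0.0819/0.9919 = 8.3%
- r=0.1, s=0.6: 0.3564/0.9964 = 35.8%
- r=0.3, s=0.6: 0.3276/0.9676 = 33.9%

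Simulating 400 cohorts per setting agrees: about 35-100% significant and 8-36% apparently mediated. The true value is 0 throughout.

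**The case against.** The strongest reply is that the text is brief and does not tie mediation to T0. The words "than the general population at the time they enroll in CHAMPS" qualify the population comparison. The mediator sentence is separate, and it names two moderators that are first measured at T1. Aim 1 never lists sleep, social support or traumatic stress as mediators, and does not say that mediators become intervention targets. Models and waves may sit in an analysis plan that is not shown.

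Part of this stands. The candidates in the illustration come from the list of instruments, not from Aim 1, and the harm is a risk, not a stated plan. But the mediator sentence sits in the aim defined by enrolment outcomes, and no later model specification can create an order that the T0 data lack.

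A reader might also infer more than the documents support:

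- **That a reversed order gives the same indirect effect.** It gives the same fit. The effects coincide only in special cases, as the second table shows.
- **That reversal explains the problem with race.** Symptoms do not cause race. Race fails because it precedes exposure.
- **That nothing can precede any Aim 1 outcome.** Substance use is measured at T1, after the T0 scales, although its question asks about change since the pandemic began and the T0 candidates are still collected together with the exposure. Some exposure items, such as a changed work setting, also report earlier events. That may help order exposure before mediator, but it does not order mediator before a T0 outcome.
- **That Aim 5 shares the fault.** It says "We will ascertain whether thematic content is a moderator or mediator of health outcomes", but does not restrict those outcomes to T0, and it already treats themes as correlates of distress. The health history checklist starts at T1, after the baseline narrative.

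**Conclusion.** The point holds in a limited form. For stress, anxiety and depression at enrolment, Aim 1 cannot establish mediation by any psychosocial variable on the schedule, and the mediator it names cannot be one. That much follows from the text and Table 1 alone.

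The figures of 35-100% and 8-36% are an illustration. They rest on assumed correlations and on a scenario in which the mediator has no effect by construction. They show how large a false pathway could be at this sample size, not how large it will be in this cohort.

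The change is worth making because the study already schedules waves that supply the missing order.

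**What to change.** 1. **Aim 1.** Remove mediation. Treat race as a covariate or a moderator. Leave proactive coping and resilience as the named moderators; limiting moderation to T0 variables would remove both.
2. **Aim 3.** Place mediation here with ordered waves: exposure at T0; mediator at T1 (burnout, eating habits) or T2 (sleep, traumatic stress); outcome at a later wave. Adjust for the T0 level of the outcome and, where one was collected, of the mediator. Burnout and eating habits have no T0 level.
3. **T0-only results.** Report them as associations, not pathways. This includes social support, which is measured only at T0 and so cannot serve as a later mediator.
4. **Aim 5.** No change on this point.

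Cost: wording of two aims and no new data. At most 1534 of 2762 participants (1534/2762 = 55.5%) can contribute, fewer after dropout. Results wait for Year 1 at the earliest with a T1 mediator, or Year 2 with a T2 mediator. Ordered waves reduce the ambiguity of direction but do not remove unmeasured confounding.
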